#### **10.3.3. Persistent Mobility Disability**

Persistent mobility disability is defined as having major mobility disability at two consecutive clinic visits.

#### **10.3.4. Self-Reported Disability**

As described in Chapter 6, the primary measures of self-reported function are the MAT-sf and the 19-item Pepper Assessment Tool for Disability (PAT-D).

In addition, for the basic ADLs the participant is also asked whether the participant receives help from another person to complete the task. This allows calculation of a Katz ADL score. The proxy ADL questionnaire is administered when a participant is not available to complete a follow-up assessment or is deemed to be cognitively impaired based on the Six-item screener.

### 10.3.5. Cost Effectiveness

**Quality-adjusted life years (QALYs)** are used for cost-effectiveness analysis. QALYs integrate mortality and morbidity to express health status in terms of equivalents of well-years of life.

Although there has been considerable interest in measuring cost effectiveness of treatments in old age, the validity of most general preference weighted measures has not been well evaluated in this field. One exception is the **Quality of Well-being Scale (QWB)**, which has been used in several trials with seniors. Studies using the QWB suggest that physical activity interventions may produce benefits for older adults at a cost comparable to many widely advocated programs. In addition to the ease with which QALYs can be calculated from the QWB-SA, the measure allows for specific areas of clinical improvement to be identified among its 58 acute and chronic symptoms.

**10.3.6. Tertiary outcomes** include (a) the combined outcome of MCI or dementia, (b) a composite measure of the cognitive assessment battery, (c) the SPPB score and 400 m walk speed assessed in ethnicity/race, gender and baseline performance subgroups; (d) time by intervention interactions on the SPPB score and 400 m walk speed endpoints; (e) sleep-wake disturbances, (f) dyspnea, (g) ventilatory capacity, (h) pulmonary events and (i) cardiovascular events.

**(a) Mild Cognitive Impairment/Probable Dementia (MCI/PD).** We will contrast the rates of all-cause MCI/PD at 2 years. While assessment of the impact of PA on the incidence of dementia and mild cognitive impairment is of great interest, LIFE may not have sufficient power for a definitive result. This outcome will therefore be explored as a tertiary aim. Cases will be identified using a **2-staged** approach similar to what has been found to be efficient in other trials of cognitive studies (Appendix A).

**Stage 1** is the LIFE cognitive screening battery (See 6.2.11) followed by a more detailed neuropsychological assessment for incident MCI or dementia. In **stage 2**, MCI/PD status will be adjudicated by an **expert panel** (masked to intervention assignment) based on all cognitive assessments (administered by centrally trained and certified staff), informant based report of functional impairment, and review of medical records.

**(b) A composite measure** derived from the cognitive assessment battery (DSST, HVLT, Flanker, N-back and Task Switching), excluding the 3MSE, will be standardized and averaged to form a single composite score for additional analysis as a tertiary outcome.

**(c) Short Physical Performance Battery (SPPB).** The SPPB, originally developed for the Established Populations for the Epidemiologic Study of the Elderly (EPESE) is a brief performance battery based on timed short distance walk, repeated chair stands and balance test (as described by Guralnik et al.)

**(d) Sleep-Wake Disturbances** will be evaluated with four validated instruments: Epworth Sleepiness Scale (ESS), Insomnia Severity Index (ISI), Pittsburgh Sleep Quality Index (PSQI), and Berlin Questionnaire (BQ).

**(e) Dyspnea.**

Dyspnea will be assessed with a modified version of the ATS-DLD-78-A questionnaire [ATS-DLD-78-A Adult Dyspnea Questionnaire. at <http://www.cdc.gov/niosh/respire.html>] and the Borg index for Dyspnea.

**(f) Ventilatory Capacity**

Ventilatory capacity will be assessed by spirometry and maximal inspiratory pressure

(MIP). Spirometry will be recorded by the EasyOne™ PLUS spirometer. MIP will be recorded by a pressure gauge fitted with a disposable cardboard mouthpiece.

**(g) Pulmonary outcomes**

Pulmonary outcomes to be assessed include hospital admission for exacerbation of airway disease (asthma, bronchitis, emphysema, &/or COPD) or pneumonia. Initial ascertainment of pulmonary hospitalizations will be made at the every 6 month follow-up interviews. Medical records will be obtained and reviewed blinded to group assignment. Details of the review and adjudication are provided below.

**(h) Cardiovascular outcomes**

Cardiovascular events to be assessed as tertiary outcomes include the combined outcome of:

- Myocardial infarction (MI),
- Angina requiring hospitalization,
- Any stroke (ischemic or hemorrhagic),
- Transitory ischemic attack (TIA) requiring hospitalization,
- Hospitalization for carotid artery disease,
- Hospitalization for congestive heart failure (CHF),
- Hospitalization for peripheral artery disease (PAD) or outpatient revascularization for PAD,
- Ruptured abdominal aortic aneurism (AAA), and
- CVD death.

Initial ascertainment of cardiovascular hospitalizations and procedures will be made at the every 6 month follow-up interviews. Medical records will be obtained and reviewed blinded to group assignment. Details of the review and adjudication are provided below.

**10.4. Outcome Adjudication Procedures**

**10.4.1. Adjudication of the Major Mobility Disability Outcome**

Final determination regarding when study participants reach the major mobility disability outcome is made by the Outcomes Committee, using an adjudication process. Final assignment of endpoint requires unanimous agreement by the committee which reviews cases at least every 6 months. In most instances, the outcome of major mobility disability is readily apparent from the results of the 400 m walk performance test. All subjects who attempt but do not complete 400 m in 15 minutes or less are categorized (on the day of the assessment) as **mobility disabled**. Any individual requiring an alternative assessment has all available records summarized and reviewed by the committee, for determination of disability status. These alternative contacts may include a home visit, telephone interview with participant or proxy, or review of hospital records.

The process of review of all alternative contacts is sensitive to cases of possible disability and minimizes loss-to-follow-up by making use of all available information. The criteria for adjudication of these potential cases as mobility disabled are designed to maximize specificity and minimize bias. There may be some cases where only self-report or proxy-report may be available. LIFE has designed an interview that is quite specific, as compared to performance testing. No self- or proxy-report instrument is perfectly sensitive and specific; hence the primary method of outcomes assessment must be based on objective performance. Those with inadequate information for a definite diagnosis of major mobility disability are considered to be non-disabled for mobility. Some may become mobility disabled by the subsequent visit. Every effort is made to obtain follow-up contact within the required time window using the same methods in both intervention groups. All

outcomes assessments are performed by researchers who are blinded to group assignment. The committee is also blinded to intervention assignment. This approach is similar to methods used for adjudication of cardiovascular disease, cancer, dementia, fracture and other health outcomes in RCTs.

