**Average Follow-up:** We assume that recruitment will take 21 months. Power is calculated under two scenarios: 1) an assumption of a uniform recruitment rate; and 2) that the recruitment rate will accelerate during these 21 months so that approximately **50%** of participants will be recruited in the first 12 months, and **50%** will be recruited in the final **9** months. Close-out visits will occur for 3 consecutive months. The first participant recruited will have a close-out visit at 42 months (3.5 years) of follow-up and the final randomized participant will be followed for 23 months (1.9 years). Using these projected recruitment rates and lengths of follow-up, the average follow-up time will be approximately 31 months.

**Observational Follow-up:** Following the completion of the study intervention period, all participants will be asked to complete an additional assessment visit approximately one year after their last assessment visit to gather additional safety data and confirm the occurrence of the persistent mobility disability outcome. This visit will be referred as the Post Intervention Visit (PIV).

**Loss to Follow-up:** In LIFE-P, 400 m walk results or definitive adjudications were obtained in 94% (6 months) and 92% (12 months) of participants. We will assume that **loss to follow-up** accumulates at **8%/yr** throughout LIFE and factor this into all projections of power below. If loss to follow-up accrues at 7%/yr or 9%/yr rather than 8%/yr, the power for detecting the specified effect sizes would be increased or decreased by only 1%.

**Inference:** Our projections are based on a log-rank test with **2-sided significance level 0.05**. We have not adjusted this for interim analyses; however, the approach we recommend (Chapter 9) will not alter the final critical value materially.

**Calculations:** We have used SAS Proc Power, to allow incorporation of the increase in event rates during follow-up years 2-3.7 into our power calculations. In using this procedure, we assumed a uniform recruitment rate over 21 months. We have used the simulation option of NQuery Advisor to allow for calculation of power assuming recruitment of 50% of participants in the final 9 months of the 21 month recruitment period.

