Of primary interest is a comparison of the probability of being classified as having major mobility disability at two consecutive assessments. This outcome will be analyzed using transitional models for categorical endpoints. A first-order Markov model will be used to compare between intervention groups the probability of being classified in the major mobility disability category at a subsequent visit, given a participant's previous classification state. Validity of the first-order versus higher-order Markov assumptions will be explored within these models.

**Secondary aim #4** will be to assess the relative effect of randomization to the intervention on the combined outcome of major mobility disability or death.

The main comparisons of intervention groups with respect to the distribution of time until the first post-randomization occurrence of the combined outcome of major mobility disability or death will be based on survival analyses. To compare intervention arms, we will use a likelihood ratio test from a Cox regression model, stratified by field center and gender. Failure time is measured from the time of randomization.

**Secondary aim #5** will be to assess the relative effect of randomization to the intervention on the proportion of 400 m walk failures over time.

This analysis will use the repeated 6-month indicators of 400 m walk status (rather than the time until the initial failure) and compare the average proportion of participants in each intervention group that fail the 400 m walk across all time points using generalized estimating equations (GEEs) that account for the dependency between repeated measures. Odds ratios for the association between 400 m walk status and intervention will be estimated after adjusting for field center, gender, a follow-up time effect, and an intervention effect. This approach is most consistent with 400 m walk serving as a marker of functional status and the trial examining whether lifestyle interventions may alter the distribution of this construct.

**Secondary aim #6** will be to assess the relative effect of randomization to the

intervention on the disability in activities of daily living.

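### A visit without enough information is classified as non-disabled, which turns missing outcome data into event-free time and is not reconciled with how section 3.3 counts loss to follow-up

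*Protocol*

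**What the plan says.** Section 10.4.1 of the protocol makes the Outcomes Committee responsible for deciding when a participant reaches major mobility disability. A participant who attempts the 400 m walk and does not finish within 15 minutes is disabled on that day. Anyone else is judged from a home visit, telephone or proxy interview, or records, against a list that contains only definite criteria. For the remainder the rule is: "Those with inadequate information for a definite diagnosis of major mobility disability are considered to be non-disabled for mobility". The next sentence adds: "Some may become mobility disabled by the subsequent visit". The same paragraph says that the review of alternative contacts "minimizes loss-to-follow-up by making use of all available information".

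Section 3.3 reports that in the pilot "400 m walk results or definitive adjudications were obtained in 94% (6 months) and 92% (12 months) of participants". From this it assumes loss of 8%/yr "throughout LIFE and factor this into all projections of power below", with 7%/yr and 9%/yr as variants.

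Section 12.2 specifies a Cox likelihood ratio test, stratified by field center and gender, with time measured from randomization. It states no censoring rule. For persistence, section 10.3.3 says: "Persistent mobility disability is defined as having major mobility disability at two consecutive clinic visits". Section 12.2 (secondary aim #3) analyses this with a first-order Markov model conditional on the previous classification.

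**The concern.** The rule assigns the favourable outcome when the outcome is not known. In a time-to-event analysis, a visit classified as non-disabled is a visit passed without the event, so the participant stays in the risk set. In the Markov model it is an observed state. Section 3.3 treats people in the same position, with no walk result and no definitive adjudication, as lost.

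The default can also catch people who were contacted. The fallback criteria describe far worse function than failing 400 m: needing more than 10 seconds for 4 m, or being unable to cross a room unaided. A participant who does not attempt the walk and covers 4 m in 8 seconds meets none of them and is non-disabled by default, whatever their 400 m ability.

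At stake is the primary hazard ratio. Defaulted visits enlarge an arm's denominator and add no events, so the arm with more of them looks better. The arms differ in intervention contact: PA has two center sessions a week throughout; SA has one a week to week 26, then two a month offered and one required. Unequal missingness is therefore plausible, though its direction is not known.

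**Working it through.** **Inputs from the protocol.** 1,600 participants, 1:1; two-sided 0.05; SA event rate 18%/yr, rising to 21%/yr after two years; uniform accrual over 21 months; follow-up 23 to 42 months; loss 8%/yr (all section 3.3, allocation from 6.4.2). **Assumed:** any split of loss by arm, and how long the default is carried.

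**Step 1: the plan's own power.** Hazards are −ln 0.82 = 0.1985/yr to year 2, then −ln 0.79 = 0.2357/yr. Loss is independent censoring at −ln 0.92 = 0.0834/yr in both arms. Follow-up is uniform from 23 to 42 months. Power = Φ(½√D·|ln HR| − 1.96), where D is the expected number of events. For a 21% effect D ≈ 564, so ½√564 × 0.2357 = 2.80 and Φ(2.80 − 1.96) = Φ(0.84) ≈ 80%.

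| Effect | 20% | 21% | 22% | 23% | 24% | 25% |
|---|---|---|---|---|---|---|
| Table 3.3.1 | 76 | 80 | 84 | 87 | 90 | 93 |
| Recomputed, loss censored | 75.7 | 80.0 | 83.8 | 87.1 | 89.9 | 92.3 |

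Loss of 7%, 8% and 9%/yr gives 80.5%, 80.0% and 79.4%, which agrees with the change of about 1% that section 3.3 states. The published power is consistent with loss handled as censoring.

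**Step 2: how the default acts.** Let arm j have event-free probability S_j(t), retention G_j(t), loss hazard l_j, and let A(t) be the fraction not yet administratively closed. If a lost participant stays event-free in the risk set for a further time c, the risk set is

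Y_j(t) = A(t)·[S_j(t)G_j(t) + ∫ l_j G_j(u) S_j(u) du], with u from max(0, t − c) to t.

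The integral adds people who cannot contribute an observed event. With c = 0 it vanishes and the Cox estimate is unbiased when loss is non-informative.

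**Step 3: size under assumed unequal loss.** Simulated trials, 800 per arm, 18%/yr SA event rate:

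| Default carried for | HR; true HR 1.0, loss 6% SA / 10% PA | Two-sided rejection | Power; true HR 0.79, loss 10% SA / 6% PA |
|---|---|---|---|
| not at all (censored) | 1.00 | 5% | 79% |
| 6 months (one visit) | 0.98 | 6% | 70% |
| 12 months (two visits) | about 0.97 | 8% | 63% |
| to study end | 0.94 | 11 to 12% | 50% |

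A separate large-sample calculation with the 18% to 21% rates agrees at the extreme: a true HR of 1.00 becomes 0.938, and the chance of wrongly declaring PA superior rises from 2.5% to 12.1%; a true HR of 0.79 becomes 0.846, with power of 51%. A milder split of 7% SA / 9% PA carried to study end turns 1.00 into 0.969.

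**Step 4: equal loss.** At 8%/yr in both arms, carrying the default to study end moves the HR from 0.790 to 0.794 and power from 80.0% to 78.3%, a cost of 1.7 points.

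**Step 5: informative loss.** With an assumed shared gamma frailty of variance 1, no true effect and 6% SA / 10% PA, censoring gives about 0.96 and the default carried to study end about 0.92. Censoring reduces this bias but does not remove it.

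**Step 6: persistence.** Take the sequence disabled, unclassified, disabled. Under the default the Markov model receives disabled, non-disabled, disabled: one recovery and one new onset, neither observed. If the middle visit is missing, no recovery is recorded.

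**The case against.** The strongest reply is that the rule sets status at one visit for someone still being followed. The sentence "Some may become mobility disabled by the subsequent visit" supports that, and the paragraph speaks of loss to follow-up as a separate matter. Censoring at the last definite assessment is compatible with this reading. This stands. A reader might infer that lost participants must be kept event-free to study end instead of being censored; the protocol does not say so, and the study-end figures are an upper end. But the visit-level reading does not clear the rule. Each defaulted visit is still event-free time, and one such visit already moves the hazard ratio to about 0.98 under the assumed split.

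Second, censoring detail often sits in the SAP. True, and its absence alone would be no finding. Here the protocol states a classification, so the point concerns what is written.

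Third, the unequal rates are invented. Correct: section 3.3 gives only 8%/yr. Assessment is six-monthly in both arms with the same methods and blinded staff, and people who stop sessions are still urged to attend assessments. Heavier PA contact would, if anything, suggest more loss in SA, which biases against PA. The direction is open, so both splits are shown.

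Fourth, the strict fallback criteria are a deliberate choice for specificity. That justifies not calling an uncertain case disabled; it does not justify calling it non-disabled.

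Three further inferences should not be drawn. The rule does not contradict the power calculation: Table 3.3.1 reproduces with loss censored, so sections 3.3 and 10.4.1 are unreconciled, not opposed. It is not shown to put false zeros into the walk-failure GEE: section 12.2 says "This analysis will use the repeated 6-month indicators of 400 m walk status", which are walk results, and nothing says that the adjudication default fills them. And no adjudication form is shown, so it cannot be assumed that indeterminate cases are already recorded separately.

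**Conclusion.** The concern holds in a limited form. Section 10.4.1 fixes a favourable default for unclassified participants, offers no missing category, and is not reconciled with section 3.3. The default enters the primary Cox model as event-free time and the persistence model as an observed non-disabled state.

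The size depends on two things that the protocol does not give: how long the default is carried and how far unclassified visits differ between arms. Under a 6%/10% split the distortion runs from small (one visit) to serious (study end), and the milder 7%/9% split roughly halves the shift at study end. With equal loss the bias is negligible. The simulations treat loss as non-informative except in Step 5, where censoring was better but not sufficient. The rule should be corrected before unblinding, because afterwards the choice between these readings could be made with knowledge of which arm it favours.

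**What to change.** In sections 10.4.1 and 12.2:

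- State that a visit without a definite classification is unclassified (missing), not non-disabled.
- State that in the primary Cox model a participant with no later definite classification is censored at the last definite assessment.
- State that an unclassified visit is treated as missing, not as non-disabled, in the Markov analysis of persistence.
- Add two sensitivity analyses, with the number of unclassified visits shown by arm: all missing set to non-disabled, and all missing set to disabled. These are needed because censoring does not deal fully with informative loss.

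The cost is a few sentences, slightly less person-time and a little more analysis work. The sponsor should check that the adjudication data separate visits judged non-disabled from visits defaulted to it; if they do not, that field has to be added.

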### **Hierarchical Adjudication of Major Mobility Disability**

**Definite:** ANY of the Following:

**(1) Primary**

Unable to complete 400-meter walk in 15 minutes without sitting or the help of another person

**(2) Alternative (in home or clinic)**

Unable to walk 4 meters without assistance of another person or use of a walker OR (or comparable device) Unable to complete 4-meter walk test in 10 seconds or less, i.e. gait speed less than 0.4 meter/sec

**(3) Alternative (telephone or in home)**

(a) Self report of inability to walk across a room (12 ft) without the assistance of another person

*Operationally, this criterion is met based on an affirmative response to one or more of the following 2 questions:*

*(i) respondent answers “unable to do” when asked, “During the past month, how much difficulty have you had walking across a small room because of your health?”*

*(ii) respondent answers “Yes” to “Do you usually receive help from another person when you walk across a small room”;*

**OR**

(b) Proxy report of inability to walk across a room (12 ft) without the assistance of another person

*Operationally, this criterion is met based on an affirmative response to the following question:*

(i) proxy answers “Yes” to “Does (participant) usually receive help from another person when he/she walks across a small room”;

**(4) Alternative (medical record)**

Documentation of inability to walk across a room (12 ft) without the assistance of another person or use of a walker (or comparable device); example of descriptors include: bed-bound or wheelchair-bound, obtunded or moribund, etc.

#### **10.4.2. Death**

The fact and date of death are confirmed by death certificate. Cause is determined from hospital records, death certificate and informant interview information and coded into major categories of death.

